#### Secondary objectives

Rates of control of VRF at baseline and outcome in each group.Proportion of participants in group I achieving VRF targets at 3, 6 and 9 months for each risk factor.Difference in mean change in MoCA score between groups C and I. The between-group comparison will be based on a general linear model with group as a fixed effect and including any prognostic variables at baseline for which there is a between-group disparity. A 95% CI for the difference in means will be constructed to give an idea of the likely magnitude of benefit from the intervention.Indicative incremental cost per point gained in MoCA, DEMQOL and per QALY gained between groups C and I. Data will be analysed in terms of costs and effects for the two groups. We will analyse key drivers of costs and examine the potential of this intervention to be cost-effective.Change in MoCA score between baseline and 12 months in group O participants, and in groups O and C combined.Difference in adverse event rates between groups.Difference in mean BP between groups C and I.Difference in BP (systolic and diastolic) variability between groups C and I.Difference in PWV between groups C and I.

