### Intermediate stage (MoCA score 20–25)

Patients will be informed of their result and asked to confirm their willingness to continue to participate in the feasibility trial. They will be randomised into one of two groups: control arm (group C) or intervention arm (group I). Randomisation will be based on computer-generated blocked randomisation managed by the Norwich CRTU.

Patients in group C will receive usual care by their clinicians and will be followed up at 12 months.

Patients in group I will undergo enhanced VRF management through assessment by the study team at 3, 6 and 9 months. Specific aims will be set for each modifiable risk factor and the GP will be informed about these targets and the results of each visit.

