#### Secondary outcome measures

Difference in mean change in MoCA score between groups C and I at 12 months;Proportions of participants in each group whose vascular risk factors are controlled at each time point;Frequency of adverse events in each group;Indicative incremental cost per MoCA point and quality-adjusted life-year (QALY) gained by the intervention;Mean change in MoCA score in group O related to number of VRF and proportion of participants whose VRF are controlled at baseline and outcome.

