### Sample size calculation

As this is a feasibility study a formal sample size calculation has not been performed. The duration and sample size of the study are based on the estimated prevalence rate of cognitive impairment at diagnosis (around 30%),^4^ incidence of dementia after the event (~30% in 3 months),^3^ estimated screening and recruitment rates. The aim is to include a minimum of 100 patients in the feasibility study (50 per group) and another 100 patients in the observational study.

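### The MoCA comparison adjusts only for baseline variables that look imbalanced after randomisation, which loses precision and makes the 95% CI somewhat too wide; fix the covariates in advance, with baseline MoCA always included

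*Protocol article*

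**What the plan says.** The outcome is listed in the protocol article under Secondary outcome measures: "Difference in mean change in MoCA score between groups C and I at 12 months". The Data analysis plan (Secondary objectives) gives the model: a general linear model with a fixed term for group, "including any prognostic variables at baseline for which there is a between-group disparity". The interval has a stated purpose: "A 95% CI for the difference in means will be constructed to give an idea of the likely magnitude of benefit".

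Four other places bear on this:

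- Intermediate stage (MoCA score 20–25): groups C and I are randomised, and no stratification factor is named that would otherwise settle the covariates. "Randomisation will be based on computer-generated blocked randomisation managed by the Norwich CRTU".
- The same section restricts both randomised groups to a baseline MoCA of 20 to 25. Table 1 marks the MoCA at screening and 12 months, so the score used for selection is also the baseline value.
- Sample size calculation: 50 per group are planned, and "As this is a feasibility study a formal sample size calculation has not been performed".
- Study objectives: estimating the sample size of the definitive trial is a secondary objective.

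No covariate is named, and baseline MoCA is not stated to be one.

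**The concern.** Between randomised groups, baseline differences arise by chance. How large a difference looks says nothing about how much of the outcome variance the variable explains, and that is what adjustment exploits. The rule discards a strong predictor that happens to balance and keeps a weaker one that does not.

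Baseline MoCA deserves particular mention. The outcome is a change score and patients are selected on the same test, so change can be expected to depend on baseline through regression to the mean. Yet baseline MoCA enters only if the arms happen to differ on it.

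The article also does not define a disparity, so the final model can be settled only once data have been seen. At stake are the width and calibration of the interval meant to show the likely benefit on cognition, and the usefulness of this analysis for planning the definitive trial.

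**Working it through.** **Plan's own figure.** There is none to reproduce: the plan states no power, effect size or SD for MoCA.

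**Inputs.** From the article: 50 per arm, 1:1 randomisation, 95% CI. Assumed, because the article gives no values: correlation |r| of each baseline covariate with MoCA change, 0.3 to 0.7 for one covariate and 0.3 or 0.4 each for five independent covariates; disparity taken as baseline p<0.05 or p<0.20. Results are in units of the SD of MoCA change.

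**Step 1: what fixed adjustment offers.** Unadjusted SE = √(2/50) = 0.200, so the CI half-width is 1.96 × 0.200 = 0.392. With one covariate always included, the half-width is 0.392 × √(1 − r²):

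- r = 0.3: 0.374
- r = 0.5: 0.339
- r = 0.7: 0.280

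**Step 2: how often the rule fires.** If a disparity means p<0.05 and there are k independent candidates, the chance of at least one is 1 − 0.95^k: 5% (k=1), 14% (k=3), 23% (k=5), 40% (k=10). This is the behaviour of correct randomisation. It depends on the assumed definition, and k counts only variables already accepted as prognostic.

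**Step 3: the rule applied mechanically.** Simulation with no treatment effect, 8,000 trials per row, 50 per arm. True SE is the spread of the estimates; reported SE is the average from the fitted model.

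| Covariates | Disparity cut | True SE, rule | Reported SE, rule | Coverage, rule | Reported SE, always adjusted |
|---|---|---|---|---|---|
| 1, r=0.5 | p<0.05 | 0.192 | 0.199 | 95.8% | 0.174 |
| 1, r=0.5 | p<0.20 | 0.184 | 0.195 | 96.2% | 0.174 |
| 1, r=0.7 | p<0.05 | 0.186 | 0.197 | 96.2% | 0.143 |
| 1, r=0.7 | p<0.20 | 0.166 | 0.189 | 97.3% | 0.143 |
| 5, r=0.3 each | p<0.05 | 0.188 | 0.199 | 96.3% | 0.152 |
| 5, r=0.3 each | p<0.20 | 0.172 | 0.194 | 97.3% | 0.152 |
| 5, r=0.4 each | p<0.05 | 0.176 | 0.197 | 97.0% | 0.092 |
| 5, r=0.4 each | p<0.20 | 0.144 | 0.185 | 98.9% | 0.092 |

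The mean error was at most about 0.003 SD, so there is no average bias. Always adjusting gave 94.7 to 95.4% coverage. With one weak covariate (r=0.3), coverage under the rule was 95.1 to 95.6%, against a simulation error of √(0.95 × 0.05/8000) = 0.24 percentage points, so any effect there is slight. Results at 40 per arm were similar. The last two rows are extreme: five covariates at 0.4 explain 5 × 0.16 = 80% of the variance.

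The interval is too wide because the rule removes the large chance imbalances, so the estimates vary less. When the covariate balances and is dropped, however, the model still charges its variance to the residual.

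**Step 4: share of the gain that reaches the interval.** At r=0.5 and p<0.20, the reported SE falls by 0.1995 − 0.1949 = 0.0046, against 0.1995 − 0.1735 = 0.0260 under fixed adjustment, or 18%. The same ratio across the table runs from about 2% to 19%. The true SE recovers more (62% in the same row, 30% at p<0.05), but the reported interval does not show it.

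**Step 5: baseline MoCA alone.** If scores are uniform on the integers 20 to 25, the variance is (36 − 1)/12 = 2.92, SD 1.71. Assume a follow-up SD of 3 and a slope b of follow-up on baseline. Baseline then explains (1 − b)² × 2.92 of the change variance, and the residual is 9 − b² × 2.92.

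- b=0.5: 0.73/(0.73 + 8.27) = 8%; CI narrower by 1 − √0.919 = 4%
- b=1: nothing
- b=0: 2.92/11.92 = 24%; CI narrower by 13%

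**Step 6: discretion.** In a worst case where the analyst picks the most favourable subset of five covariates (r=0.3 each) after seeing results (2,000 trials), the null estimate is biased by about 0.12 SD and non-coverage is about 8.7%.

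**The case against.** The strongest reply is that little depends on this. The primary outcome is recruitment and retention, MoCA change is one of several secondary outcomes, and the plan ties no test or decision rule to it. The rule errs on the cautious side, and for weak covariates the error is trivial. A threshold and candidate list may also stand in an analysis plan that is not shown. All of this stands and limits the severity. It does not rescue the rule: a definition of disparity elsewhere would still select on imbalance.

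It is also fair that the rule asks for variables to be prognostic as well as imbalanced, and that a marked baseline MoCA difference would bring baseline MoCA into the model. What remains unadjusted is differences too small to count. Step 5 shows that, within 20 to 25, baseline MoCA alone may add little precision, so calling it a strong predictor would go beyond the documents.

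A reader might infer that the interval is too narrow, the estimate biased, or the false-positive rate near 9%. The documents do not support this. Those results need covariates chosen in the light of outcomes, whereas the stated rule conditions on baseline values only. Nor is this the trial's only effect estimate: the same section lists BP, BP variability, PWV and adverse event comparisons.

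**Conclusion.** The point holds, at moderate weight: it should be fixed, but it does not threaten the feasibility aims. The stated rule selects covariates on chance imbalance. Used mechanically it gives an estimate that is unbiased on average, a 95% CI that is somewhat too wide (about 95.5 to 99% coverage, close to nominal for a single weak covariate), and a reported SE that shows at most about a fifth of the available gain in the scenarios tabulated. Those sizes rest on assumed correlations, candidate numbers and disparity thresholds, none of which the article gives. The undefined disparity leaves room for discretion, but error above 5% would follow only if that room were used with the results in view. It matters because this is the between-arm estimate of effect on cognition, and planning the definitive trial is a stated objective.

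**What to change.** Drop the disparity rule. Analyse 12-month MoCA by ANCOVA with arm, baseline MoCA always included, and a short fixed list of prognostic variables already available, for example age (listed under baseline demographics) and stroke versus TIA (known from eligibility). Using change as the outcome gives the same arm estimate once baseline MoCA is in the model. Set the list before follow-up closes in July 2018 and do not alter it for observed balance. Time from event to MoCA is not among the listed baseline items, so include it only if it was recorded. Report the unadjusted difference as a sensitivity analysis.

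The cost is one sentence in the analysis plan and a few degrees of freedom, with no new data. If the fixed covariates prove weak, the gain will be small, but the interval will have its stated coverage.

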### Study objectives

The primary objective of the study is to determine the feasibility of randomising patients who have signs of early cognitive decline, but no dementia, into routine risk factor management or enhanced risk factor management by their GP, and to assess adherence to the proposed intervention by enrolled participants.

The secondary objectives are as follows:Determine the potential clinical benefit of enhanced control of VRF in preventing progression of cognitive decline and the development of dementia poststroke/TIA.Assess indicative cost-effectiveness of this intervention.Estimate the sample size for a future definitive multicentre randomised controlled trial.Identify any adverse events due to the intervention, including rates of recurrent stroke/TIA.Explore the incidence of cognitive impairment on longitudinal follow-up in a UK population after stroke/TIA with current routine risk factor management.

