### Ordering of assessments

The following assessments will be carried out on all participants at baseline (table 1):Eligibility assessment and informed consent;MoCA;Demographics, including age, gender, body mass index, smoking status, alcohol consumption and exercise habits;Assessment of past medical history, including VRF;Record concomitant medications.

**Table 1 T1:** Summary of study procedures

Procedures for all participants	Visits					
	Screening	Baseline	3 months	6 months	9 months	12 months
Eligibility assessment	✓	✓	–	–	–	✓
Informed consent	✓	✓	–	–	–	–
Montreal Cognitive Assessment	✓	–	–	–	–	✓
Medical history	✓	–	–	–	–	–
Demographics	–	✓	–	–	–	–
Concomitant medications	–	✓	–	–	–	✓
Physical examination including VRFs	–	✓	–	–	–	✓
Blood sample for cholesterol±INR and blood glucose/HbA1c	–	✓	–	–	–	✓
Adverse events	–	–	–	–	–	✓
Additional procedures for participants in group C						
24-hour BP measurement	–	✓	–	–	–	✓
Beat-to-beat BP measurement	–	✓	–	–	–	✓
Pulse wave velocity measurement	–	✓	–	–	–	✓
Quality of life and functional assessment*	–	✓	–	–	–	✓
Resource use questionnaires	–	✓	–	–	–	✓
Additional procedures for participants in group I						
Eligibility assessment	–	–	✓	✓	✓	–
Assessment of VRFs	–	–	✓	✓	✓	v
Blood sample for cholesterol±INR and blood glucose/HbA1c	–	–	✓	✓	✓	–
Concomitant medications and adherence	–	–	✓	✓	✓	–
Quality of life and functional assessment*	–	✓	–	–	–	✓
Resource use questionnaires	–	✓	–	–	–	✓
24-hour BP measurement	–	✓	–	–	–	✓
Beat-to-beat BP measurement	–	✓	–	–	–	✓
Pulse wave velocity measurement	–	✓	–	–	–	✓
Adverse events	–	–	✓	✓	✓	–

*Includes EQ5D, Dementia Quality of Life measure, Geriatric Depression Scale, Bristol Activities of Daily Living, Morisky Medication Score.

BP, blood pressure; HbA1c, haemoglobin A1c; VRF, vascular risk factor.

In addition, participants in groups C and I will complete at baseline:EQ5D (a generic health-related quality of life questionnaire), DEMQOL (Dementia Quality of Life measure), GDS (Geriatric Depression Scale questionnaire), Bristol Activities of Daily Living questionnaire and Morisky Medication Adherence Score;Resource use questionnaires;BP variability measures including 10 min of continuous beat-to-beat BP recording and 24-hour BP monitoring;Pulse wave velocity (PWV) measurements (which reflect arterial stiffness).

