Participants in group I will be seen at 3, 6 and 9 months at which time they will have assessment of their VRF and data collection for adverse events, including recurrent stroke/TIA.

All participants will be followed up at 12 months at which time they will have:MoCA;Assessment of VRF;Recording of concomitant medications;Data collection for adverse events, including recurrent stroke/TIA.

In addition, participants in group C and I will complete at 12 months:EQ5D, DEMQOL, GDS, Bristol Activities of Daily Living questionnaire and Morisky Medication Adherence Score;Resource use questionnaires;BP variability measures;PWV measurements.

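### Adverse events are collected at four visits in group I and one in group C, so the planned unrestricted difference in rates mixes treatment effect with unequal ascertainment

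*Protocol article*

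**What the plan says.** Three places in the protocol article make adverse events a matter of comparison. Study objectives includes: "Identify any adverse events due to the intervention, including rates of recurrent stroke/TIA". Secondary outcome measures has: "Frequency of adverse events in each group". The Data analysis plan, under Secondary objectives, has: "Difference in adverse event rates between groups". None of them restricts the events by collection point, type or source.

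The collection schedule differs between the randomised arms. In Table 1 the adverse event row for all participants is ticked at 12 months only. A second adverse event row, under "Additional procedures for participants in group I", is ticked at 3, 6 and 9 months. The text under Ordering of assessments agrees: at the three interim visits group I participants are seen and "they will have assessment of their VRF and data collection for adverse events, including recurrent stroke/TIA", and the 12-month collection applies to everyone. For the control arm, the section on the intermediate stage says: "Patients in group C will receive usual care by their clinicians and will be followed up at 12 months". No study contact with group C is described between baseline and month 12.

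**The concern.** Attributing events to the intervention requires that both arms had the same chance of having an event recorded. Here group I is asked four times, with at most about three months to cover each time, and group C is asked once about a year. Mild, self-limiting or unreported events are the ones most likely to be picked up by frequent questioning and lost over a long interval.

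Two features of the trial make this more plausible. The randomised participants have MoCA scores of 20–25, so reliance on their own account of a whole year would be weaker than usual. The trial is also open-label, and the blinding described covers repeat cognitive testing only.

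An excess of recorded events in group I could then look like harm from enhanced management. For events without hospital contact, it could also hide part of a real reduction. Either would be an unhelpful message to carry into planning the definitive trial.

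**Working it through.** The plan states no adverse event rate, power or test, so there is no figure of its own to reproduce.

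**Step 1: count the collection points (Table 1 and Ordering of assessments).**

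| Group | Visits with adverse event collection | Number | Longest interval to cover |
|---|---|---|---|
| I | 3, 6, 9, 12 months | 4 | about 3 months |
| C | 12 months | 1 | 12 months |
| O | 12 months | 1 | 12 months |

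**Step 2: compare with how the plan treats other measures.** MoCA, 24-hour and beat-to-beat blood pressure, pulse wave velocity, quality of life and resource use are all scheduled identically in C and I. Vascular risk factors are also assessed at the interim visits in group I. For those, the Data analysis plan reports control in each group at baseline and outcome, and lists target achievement at 3, 6 and 9 months separately for group I. Adverse events have the same asymmetric schedule but no such separation.

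**Step 3: illustrate the size.** If the true rates are equal, the expected ratio of recorded rates is

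ratio I:C = capture over 3-month intervals ÷ capture over 12 months.

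The article gives no capture proportions, so all of the following are assumptions.

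- Complete capture in both arms: 1.00/1.00 = 1.0
- 90% and 80%: 0.90/0.80 = 1.13
- 95% and 80%: 0.95/0.80 = 1.19
- 90% and 50%: 0.90/0.50 = 1.80
- 95% and 50%: 0.95/0.50 = 1.90

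The range is therefore 1.0 with complete capture, and about 1.1 to 1.9 over the assumed incomplete values.

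**Step 4: check with a different model.** Assume that events are uniform over the year and that the probability of capture at the next visit falls as exp(−kt), with t in years since the event. Mean capture over an interval L is (1 − exp(−kL))/(kL), with L = 0.25 in group I and L = 1 in group C.

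| k (assumed) | Capture I | Capture C | Ratio I:C |
|---|---|---|---|
| 0 | 1.000 | 1.000 | 1.00 |
| 0.5 | 0.940 | 0.787 | 1.19 |
| 1 | 0.885 | 0.632 | 1.40 |
| 2 | 0.787 | 0.432 | 1.82 |
| 3 | 0.704 | 0.317 | 2.22 |

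For k from 0.5 to 2 the ratios fall within the range of step 3; at k = 3 the ratio exceeds it. With 50 per arm (Sample size calculation), one true event per person-year (assumed) and k = 1, the expected recorded events are 50 × 0.885 = 44 in group I and 50 × 0.632 = 32 in group C, with no true difference.

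**The case against.** The strongest reply is that the article does not say how the 12-month data are obtained. A reader might infer that group C must recall a whole year unaided. The text names no source, and patient report, GP or hospital records, or a combination would all fit. Source and reporting procedures are commonly left to a full protocol. If records are searched completely for the year, the bias is zero. This stands, and it is why the size cannot be fixed from the document.

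It can also be said that the analysis item is one short line with no model or test, unlike the MoCA comparison, which has a general linear model and a 95% confidence interval. How adverse events are summarised may well be set out in an analysis plan that is not shown. That is fair for presentation details. It does not remove the point, because the unequal schedule and the between-group difference are both stated in this article.

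A further reply is that the extra visits are part of the intervention, so some asymmetry is inherent in comparing enhanced follow-up with usual care. That explains the schedule, but it does not make the recorded rates comparable.

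Finally, a reader might infer that the trial's safety conclusions, or its value for planning, are undermined. The documents do not support that. The primary outcome is recruitment and retention, no progression criterion depends on the adverse event difference, and recurrent stroke/TIA leading to hospital contact is less exposed to the problem.

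**Conclusion.** The point holds as a should-fix matter on a secondary outcome. The four-versus-one schedule is exact and is stated consistently in Table 1 and the text. An unrestricted difference in rates cannot separate an effect of the intervention from differential ascertainment, and the likely direction is more recorded minor events in group I.

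The size is not known. The I:C ratio is 1.0 if the 12-month collection is complete for the year, and about 1.1 to 1.9 under assumed capture of 90–95% over three months and 50–80% over twelve. These figures illustrate what could happen and are not estimates for this trial. Nor do the documents support quoting a false-positive rate, since no significance test of adverse events is planned.

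**What to change.** Change the wording of the adverse event analysis as follows.

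1. Base the between-group difference on events ascertained in the same way in both arms. These are either events from the shared 12-month collection, provided that it covers the full year in both arms, or events from records reviewed identically in both arms. Hospital records would be one example, for recurrent stroke/TIA, admissions and deaths.
2. List events known only from the 3, 6 and 9 month visits separately and descriptively for group I, as the plan already does for risk factor targets.
3. Give all-source rates by group as well, with a caveat that ascertainment was unequal.

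The cost is mainly analysis wording, plus a record review if that route is taken. Some minor group I events leave the comparison and appear only in the listing. Equality is also not perfect, because earlier questioning of group I may help its recall at 12 months.

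A new 12-month questionnaire is less attractive. Recruitment began in November 2015, so 12-month visits would have started around November 2016, and a form introduced later would treat early and late participants differently. If the 12-month form used so far asked group I only about the time since the previous visit, the identical record review is the better basis.

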### Interventions to be measured

#### Blood pressure

Existing evidence demonstrates that lowering of BP consistently and continuously reduces cardiovascular risk. This is supported by the Royal College of Physicians (RCP) guidelines’ aim for BP <140/90 mm Hg, with an ideal target BP <130/80 mm Hg for secondary prevention.^29^ The effect of intervention on BP reduction using 24-hour BP measurement at the beginning and end of the study will be examined. This will be recorded using a SpaceLabs 90 207 monitor programmed to measure BP at 20 min intervals during the daytime (07:00–22:00 hours) and hourly overnight (22:00–07:00 hours).

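### BP, BP variability and PWV are listed as plain differences between groups C and I with no baseline term, although the stated aim is BP reduction and baseline values exist in both arms

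*Protocol article*

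**What the plan says.** The Data analysis plan (Secondary objectives) ends with three one-line items: "Difference in mean BP between groups C and I", "Difference in BP (systolic and diastolic) variability between groups C and I" and "Difference in PWV between groups C and I". None names a time point, a baseline value, a covariate or a model.

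The same list treats MoCA differently. That item is worded as a difference in mean change, and it carries a "general linear model with group as a fixed effect and including any prognostic variables at baseline for which there is a between-group disparity".

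The Blood pressure section states the aim for BP in other terms: the effect on lowering BP is to be examined from 24-hour recordings made at the start and the end of the study.

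The baseline data exist. Under Ordering of assessments, "participants in groups C and I will complete at baseline" is followed by a list that includes "BP variability measures including 10 min of continuous beat-to-beat BP recording and 24-hour BP monitoring" and PWV. Table 1 marks all three procedures at baseline and at 12 months for both groups.

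**The concern.** The BP aim refers to baseline, while the listed BP analysis, read on its face, compares levels. The authors wrote change where they meant it, for MoCA, so the missing word in the BP item cannot simply be assumed. An analyst could follow either text and produce a different estimate with a different confidence interval. For BP variability and PWV there is no second statement to conflict with, but the same gap exists: baseline values are collected in both arms and the listed comparison does not say how they enter.

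Two things are at stake. One is the precision of a secondary estimate from about 50 patients per arm. The other is how far a chance imbalance in baseline BP carries into it. The MoCA model would not settle the matter if it were borrowed, because it admits a baseline variable only when the arms are seen to differ on it.

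**Working it through.** The plan states no precision or power figure for these measures, so there is none to reproduce.

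**Inputs**
- n = 50 per arm (Sample size calculation).
- SD of 24-hour systolic BP: not in the document; 13 mmHg assumed, with 12 to 15 as a range.
- r, the correlation between baseline and 12-month values: not in the document; 0.6 to 0.7 assumed, with 0.3 to 0.8 as a range.
- Equal SD at both times, and the normal quantile 1.96.

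**Formulas for the 95% CI half-width**
- 12-month values only: H = 1.96 × SD × √(2/n)
- Change score: H × √(2(1 − r))
- ANCOVA on baseline: H × √(1 − r²)

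**With SD 13:** H = 1.96 × 13 × √(2/50) = 1.96 × 13 × 0.2 = 5.10 mmHg.

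| r | 12-month only | Change score | ANCOVA |
|---|---|---|---|
| 0.3 | 5.10 | 5.10 × 1.183 = 6.03 | 5.10 × 0.954 = 4.86 |
| 0.6 | 5.10 | 5.10 × 0.894 = 4.56 | 5.10 × 0.800 = 4.08 |
| 0.7 | 5.10 | 5.10 × 0.775 = 3.95 | 5.10 × 0.714 = 3.64 |

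**Range for SD 12 to 15:** 12-month only, 4.70 to 5.88 mmHg. ANCOVA, 4.49 to 5.61 at r = 0.3, 4.07 to 5.09 at r = 0.5, 3.36 to 4.20 at r = 0.7 and 2.82 to 3.53 at r = 0.8.

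**Variance ratios, which do not depend on the SD**
- 12-month only against ANCOVA, 1/(1 − r²): 1.56 at r = 0.6 and 1.96 at r = 0.7, but only 1.10 at r = 0.3.
- Change score against ANCOVA, 2/(1 + r): 1.25 at r = 0.6 and 1.18 at r = 0.7.

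The same ratios apply to BP variability and PWV for whatever r holds there.

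**Chance imbalance.** The standard error of the baseline difference is 13 × 0.2 = 2.6 mmHg. An imbalance of that size shifts the 12-month-only difference by r × 2.6 = 1.6 to 1.8 mmHg for r of 0.6 to 0.7. It shifts the change-score difference the other way, by (1 − r) × 2.6 = 1.0 to 0.8 mmHg. ANCOVA removes the linear part of it.

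**The case against.** The strongest reply is that the three items are labels, not an analysis specification. A condensed article commonly leaves models for exploratory measures to a SAP or full protocol, and neither is shown here. The Blood pressure section also shows that baseline BP is meant to be used. If that means a change score, ANCOVA gains only 4.56 − 4.08 = 0.5 mmHg at r = 0.6 and 3.95 − 3.64 = 0.3 mmHg at r = 0.7. Moreover, mean BP, BP variability and PWV do not appear under Secondary outcome measures, where risk-factor control is judged by the proportions controlled.

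Most of this stands, and it sets the priority. A reader might infer that the plan fixes an unadjusted comparison of 12-month values; it does not. Nor is BP lowering presented as the main check on the intervention. What remains is that two statements in the document describe the BP comparison differently, and that the list itself separates change from level.

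A reader might also infer that the ambulatory schedule distorts the 24-hour means. It gives 15 × 3 = 45 daytime and 9 × 1 = 9 night readings, so daytime makes up 45/54 = 83.3% of readings against 15/24 = 62.5% of hours. That is a sampling schedule; no rule for averaging is stated. Even an unweighted mean would shift both arms alike: the contrast moves by 0.208 × the between-arm gap in day-night fall, or 0.4 mmHg for a gap of 2 mmHg and 1.0 mmHg for a gap of 5. Likewise, the variability measure is not said to be the SD of all ambulatory readings, and beat-to-beat recordings are listed among the variability measures.

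**Conclusion.** The point holds in a limited form. The listed BP comparison does not match the stated aim of examining BP reduction, and none of the three items says how the available baseline values are used. ANCOVA on the baseline value improves on both plausible readings under the assumed SD of 13 mmHg, 50 analysed per arm and r of 0.6 to 0.7. Its half-width is 4.1 to 3.6 mmHg, against 5.1 for 12-month values alone and 4.6 to 3.9 for change scores. If r is near 0.3, the gain over 12-month values alone is small (4.9 against 5.1). With fewer patients analysed, say 40 per arm, every half-width grows by √(50/40) = 1.12 and the ranking is unchanged.

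The document does not support a claim that precision has been lost or that 24-hour means are biased. Either would depend on choices that the text does not make. This is a low-priority correction to secondary analyses in a feasibility trial.

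**What to change.** Reword the three items so that the 12-month value of each measure (24-hour BP, BP variability, PWV) is compared between groups C and I by ANCOVA, with the baseline value of that same measure as a covariate. Include it whether or not the arms appear to differ at baseline. Report the adjusted difference with its 95% CI. For BP, this brings the analysis list into line with the aim in the Blood pressure section.

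Optionally, add a sentence saying how the ambulatory readings are summarised, either time-weighted over 24 hours or as separate day and night values, and which recording supplies each variability measure.

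The change costs wording only, since every value is already scheduled at both visits. It should be made before the 12-month data are compared by arm.
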